## Abstract

Although clinical decision support systems (CDSSs) are increasingly emphasized as
one of the possible levers for improving care, they are still not widely used
due to different barriers, such as doubts about systems’ performance, their
complexity and poor design, practitioners’ lack of time to use them, poor
computer skills, reluctance to use them in front of patients, and deficient
integration into existing workflows. While several studies on CDSS exist, there
is a need for additional high-quality studies using large samples and examining
the differences between outcomes following a decision based on CDSS support and
those following decisions without this kind of information. Even less is known
about the effectiveness of a CDSS that is delivered during a grand round routine
and with the help of socially assistive humanoid robots (SAHRs). In this study,
200 patients will be randomized into a Control Group (i.e. standard care) and an
Intervention Group (i.e. standard care and novel CDSS delivered via a SAHR).
Health care quality and Quality of Life measures will be compared between the
two groups. Additionally, approximately 22 clinicians, who are also active
researchers at the University Clinical Center Maribor, will evaluate the
acceptability and clinical usability of the system. The results of the proposed
study will provide high-quality evidence on the effectiveness of CDSS systems
and SAHR in the grand round routine.

## Introduction

Clinical practice and clinical decision-making go hand in hand; it is virtually
impossible to conduct work as a clinician and avoid making decisions that require
practical application of clinical knowledge, problem-solving, weighing of
probabilities, and balancing the risks and benefits of these decisions.^
1
^ Although decision-making is an inherent part of clinical practice, it is
notoriously complex, as it consists of several, often complex and multi-target
interventions, that need to be performed within the bounds of human capabilities as
well as limits imposed by the modern health care system.^
2
^ Some of the specific challenges include (but are not limited to) the pressure
to find the optimal solution, clinicians’ tiredness and uncertainty, proneness to
heuristics and biases, information overload, inadequate staffing, and time
constraints.^3,4^
Hence, it is not very surprising that a range of errors with varying severity can occur.^
5
^ During hospitalization, specifically, these most often include medication
errors, such as dosing errors and medication omissions.^6,7^

Computerized clinical decision support systems (CDSSs) represent a paradigm shift in
improving complex healthcare today.^
8
^ CDSSs refer to any electronic system designed to aid clinical
decision-making, in which characteristics of patients are used to generate
patient-specific assessments or recommendations that are then presented to
clinicians for consideration.^
9
^ CDSSs are increasingly emphasized as one of the possible levers for improving
care. For example, they have previously been linked to reduced medication errors,
better accessibility and visibility of data, and faster prescribing of medication
and treatment^10–13^. CDSS systems can be
subdivided “knowledge-based” (i.e. rule-based) and “non-knowledge-based” (i.e.
data-driven) with regards to how the medical knowledge is catured.^8,14^ Knowledge-based systems are
workflow-driven and depend on expert rules that are used to process input data in
order to produce an action or output. The rules are based on the extensive,
subject-specific, clinical knowledge taken from the medical literature (i.e.
literature-based), clinicians, and experts (i.e. practice-based), or
patient-directed evidence.^
15
^ The non-knowledge-based systems are case-driven, however, they still require
a data source. In fact, large sets of labeled data are required to train the algorithms.^
16
^ Namely, the “decisions” in the non-knowledge-based systems do not follow
expert medical knowledge but leverage artificial intelligence (AI), machine
learning, or statistical pattern recognition.^8,14^ The non-knowledge-based
systems can simplify the knowledge acquisition and maintenance process.^
17
^ Such systems can even improve the accuracy and speed of diagnosis by
analyzing complex patterns in high-dimensional data well beyond human
performance^18–20^. However, in
healthcare, where mistakes can cost human life, the non-explainable (i.e. black-box)
nature of AI makes it unacceptable for clinicians and even regulators.^
21
^ In addition to doubts about systems, other barriers, such as lack of
transportability and interoperability, their complexity and poor design (i.e. poor
data quality and interpretation), privacy concerns and reluctance to use them in
front of patients, poor computer skills and literacy, and deficient integration into
existing workflows, prevent a wide adaption in practice.^8,10,22–24.^

As the benefits of CDSS can improve patient outcomes, it is vital to convert the
barriers described above into facilitators of CDSSs’ use^25–27^. Hence, the present study
protocol proposes the evaluation of a new system, developed with the aim to provide
an information-rich, valid, safe, and easy-to-use tool that is well-integrated into
the existing healthcare routine. The system will exploit patient-reported data,
electronic health records (EHRs), and patient-reported outcomes (i.e. pain and
psychological distress). The most prominent contribution of the proposed CDSS lies
in its format of delivery and implementation. Specifically, the CDSS will be able to
detect, as well as communicate, alarming situations (e.g. deviations in pain scores,
heart rate, and blood pressure) during grand rounds and pre/post-operative care of
patients with vascular and thoracic conditions. To this end, a fuzzy logic
(FL)-based CDSS will be deployed. FL provides a transparent (explainable) and
effective means for dealing with uncertainties in the health decision-making
process.^28,29^ The rules will be defined based on expert knowledge and already
established clinical guidelines and observations. Namely, the diseases were chosen
as they are highly prevalent, have a typically complicated course of the disease, as
there are multiple treatment options available and a lot of input information must
be monitored.^
30
^ Furthermore, the newly developed CDSS will provide intuitive visualizations
of patients’ health-related data, including EHRs, health quality measures (i.e.
pain, blood pressure, oxygenation, and heart rate), patient-reported data, and
patient-reported outcomes. The health data will be structured in an interoperable
HL7-FHIR format.^
31
^ The real-time access during the grand round routine is ensured with
speech-enabled user interfaces delivered via a tablet attached to the socially
assistive humanoid robot (SAHR), Pepper.^
32
^ While the uptake of SAHR in clinical practice is so far limited,^
33
^ and to our best knowledge, there are no studies on the integration of CDSSs
and social robotics yet, such innovative delivery could have several important
benefits. In particular, it could make the use of a CDSS more effortless for
clinicians (e.g. due to the robot being capable of movement, carrying the tablet,
and offering assistance with queries in natural language) as well as more
satisfactory and engaging for all involved stakeholders including
patients.^34,35^ It could serve as an enabler of real-time querying and
visualization of patient data.^
36
^ Adding human characteristics to the CDSS could contribute to higher trust in
the system.^33,37,38^

We hypothesize that clinicians will accept the CDSS and recognize its clinical
usability (H1). The use of CDSS will have a positive impact on health quality
measures (H2) and the quality of life of patients (H3). In addition to our primary
hypotheses, we aim to explore the impact of real-time access to the extended
clinical background on diagnostic and treatment workflows for patients with vascular
and thoracic diseases and conditions (R1).

## Methods

### Study design

The proposed study is designed as an experimental, prospective randomized
controlled clinical trial. Participants of the study, that is patients with
vascular or thoracic diseases, and clinicians, will be recruited at the regional
university clinical center. The study will be carried out in one-week intervals
over a two-year period, with one-week wash-out period between each iteration.
Clinicians will be participating in the study over the whole two-year period,
while patients will be participating only during their stay at the hospital.
During wash-out period, the CDSS and SAHR are not used in the departments. The
study will be carried out and reported on individually for the two cohorts. At
the end of the study, the results will be cross-compared to assess possible
generalizability across surgery settings.

Patients admitted to vascular or thoracic surgery wards for an elective
(non-emergency) procedure will be screened for eligibility regarding the
inclusion and exclusion criteria. Eligible participants will then be informed
about the study characteristics and asked to fill out an informed consent form.
Those who will consent to participate in the study will participate for five
days (one week) and will be randomized by the clinicians into: Intervention Group (CDSS delivered by SAHR is actively used), andControl Group (CDSS is not used; instead, only standard workflow and
progression charts are utilized).

Blinding will be achieved by handling the same tools during the grand rounds.
However, in the control group, the robot and tablet will not provide any
information to clinicians. Blinding will be furthermore achieved by adhering to
the usual workflow and paper progression charts with all patients in both
groups. The study procedure is outlined in Figure 1.

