### Participants and recruitment

The proposed study intends to recruit two distinct samples: patients and
clinicians. The patient sample will be composed of patients admitted to vascular
surgery or thoracic surgery wards for an elective (non-emergency) procedure.
Patients will need to be aged 18 years or above and willing to participate in
the study. Exclusion criteria include emergency patients, patients already
enrolled in other studies, patients with dementia, patients with special needs
or appointed guardians, and patients allocated to an intensive step-down unit
and/or regimen. The sample of clinicians will be composed of clinicians
participating in a grand round routine within the vascular surgery or the
thoracic surgery ward. Again, only employees aged 18 years or above, who will
have signed a consent form, will be eligible to participate in the study.

There will be a pool of 400 eligible participants (200 per ward) available for
inclusion in this study. Vascular and Thoracic Surgery Wards at the University
Clinical Center Maribor treat over 4000 individuals annually and it is estimated
that roughly 1400 individuals meet the inclusion criteria. However, based on the
fact that, in general, at most 30% of participants (or less) consent to the
clinical study,^
39
^ we assume that the final number of subjects willing to participate will
be much lower. Regarding sample size requirements for the present study, public
registries of clinical trials were reviewed. ClinicalTrials.gov returned 12
studies using the keywords “Vascular Diseases,” “CDSS,” and “randomized clinical
trial,” while ISRCTN and EU Clinical Trials Registers returned no studies under
the same conditions. These studies primarily focused on Stroke Prevention, CVD
Risk Factor Control, and Hypertension. These studies differed substantially in
the number of participants enrolled, from 40 to 400,000 participants per study.
Considering the tertiary settings, the studies involved between 40 and 400
participants, with an average of 80 patients. In this study, 100 patients
treated for Vascular Diseases will be enrolled in the study. Only one study was
found on ClinicalTrials.gov using keywords “Thoracic Diseases,” “CDSS,” and
“randomized clinical trial” involving 47 participants, while ISRCTN and EU
Clinical Trials Registers returned no studies under the same conditions. In this
study, 100 patients treated for Thoracic Diseases will be enrolled.

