Additionally, we also performed calculations using the G*Power software.
Patient-related analyses will predominantly be based on the ANOVA repeated
measures statistical test with the within-between interaction (two groups, two
measurements). As we hypothesize a small effect size
(*f* *=* 0.10) and intend to use a
conventional significance threshold and power (α = 0.05, 1-β = 0.80), the total
sample size needed to detect the effects is 200 participants.

The clinicians will be included in the study with the within-subjects design,
whereby they will fill out the questionnaires five times during the study
period. As such, we performed the sample size calculation in the G*Power
software, choosing the Repeated Measures ANOVA test as the statistical test,
entering a medium effect size (*f* = 0.25), and choosing a
conventional significance threshold and power (α = 0.05, 1-β = 0.80). Such
calculations suggest that at least 21 clinicians must be recruited overall.

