### Analyses of patient-related outcomes

The impact of CDSS use on the first patient-related outcome, that is health
quality measures (H2), will primarily be analyzed with growth curve
analyses.

The impact of CDSS use on the second patient-related outcome, that is perceived
quality of life (H3), will primarily be analyzed with repeated-measure analysis
of variance (ANOVA), with time as the within-subjects factor (T1 and T2; see
Figure 1).
Significant results will be followed up with pairwise post-hoc tests using the
correction to adjust for multiple testing. All results will be accompanied by
effect sizes.

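### The stated 80% power needs all 200 patients in one analysis, but the trial is to be reported separately for two cohorts of 100, each with about 51% power if the correlation is 0.5

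*Protocol article*

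**What the plan says.** **Sample size.** Under Participants and recruitment, the patient calculation is for an ANOVA repeated "measures statistical test with the within-between interaction (two groups, two" measurements), with f = 0.10 and a "conventional significance threshold and power (α = 0.05, 1-β = 0.80), the total" "sample size needed to detect the effects is 200 participants". Ward is not a factor in this calculation.

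**Split by ward.** The same section plans 100 vascular patients and says that in this "study, 100 patients treated for Thoracic Diseases will be enrolled". Each 100 is set against the size of registered trials (an average of 80 patients in tertiary settings for vascular disease, and one trial of 47 for thoracic disease). No power is given for either ward.

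**Reporting unit.** The Study design section says that the "study will be carried out and reported on individually for the two cohorts". It adds that, at "the end of the study, the results will be cross-compared to assess possible" generalizability between surgical settings. That sentence shows that the cohorts are the two wards, not patients and clinicians.

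**Analysis.** Under Analyses of patient-related outcomes, quality of life (H3) is tested by repeated-measures ANOVA at T1 and T2. The text mentions neither ward nor pooling. The Abstract speaks of 200 patients randomized to two groups, with outcomes compared between those groups.

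**The concern.** The only power figure for patients belongs to an analysis of 200, while the only reporting unit that the article names contains 100. If the trial is analysed as the Study design section describes, each cohort report has far less power than the reader is told.

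Two things are at stake. A cohort result that is not significant would be read against a claimed power of 80% and taken as better evidence of no effect than it is. And the question whether findings carry over from one ward to the other would rest on two underpowered results, with no stated contrast between them.

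**Working it through.** **Inputs from the article:** two groups, two measurements, f = 0.10, α = 0.05, power 0.80, stated total N = 200, and 100 patients per ward.

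**Inputs assumed:** the correlation ρ between T1 and T2 is not stated, so 0.5 is used first and then varied. Allocation is taken as 1:1, and sphericity is no issue with two measurements.

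**Formula.** For the within-between interaction with k = 2 groups and m = 2 measurements, the test is F with df₁ = (k − 1)(m − 1) = 1 and df₂ = (N − k)(m − 1) = N − 2. The noncentrality is λ = f²·N·m/(1 − ρ).

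**Step 1: reproduce the plan's figure.**
- N = 200, ρ = 0.5: λ = 0.01 × 200 × 2/0.5 = 8, df = 1 and 198, power = 0.804.
- N = 198, ρ = 0.5: λ = 7.92, power = 0.7997.

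So 200 is the smallest even total that reaches 0.80. With ρ = 0.49 the total would be 204, and with ρ = 0.51 it would be 196. The article's own number therefore fixes its unstated correlation at about 0.5.

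**Step 2: same inputs, one cohort.**
- N = 100, ρ = 0.5: λ = 0.01 × 100 × 2/0.5 = 4, df = 1 and 98, power = 0.508.

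**Step 3: range over ρ, with f held at 0.10.**

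| ρ | N needed for 0.80 | Power, N = 200 | Power, N = 100 |
|---|---|---|---|
| 0.3 | 278 | 0.66 | 0.39 |
| 0.5 | 200 | 0.80 | 0.51 |
| 0.6 | 160 | 0.88 | 0.60 |
| 0.7 | 120 | 0.95 | 0.72 |
| 0.8 | 82 | 0.99 | 0.88 |

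A cohort of 100 passes 0.80 at ρ = 0.8, but at that correlation the calculation would have returned 82, not 200.

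**Step 4: in units of the outcome.** An interaction of f = 0.10 in a 2 × 2 layout means cell effects of ±0.10 SD. The between-arm difference in change is therefore 4 × 0.10 = 0.40 SD. For 80% power with N = 100 and ρ = 0.5, f must be 0.141, which is a difference of 4 × 0.141 ≈ 0.57 SD. To keep f = 0.10, each ward needs 200 patients, 400 in all.

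**Step 5: what two cohort tests would show if the true effect were the same in both wards.** The wards contain different patients, so the two tests are treated as independent.
- Both significant: 0.508² = 0.26.
- Exactly one significant: 2 × 0.508 × 0.492 = 0.50.

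This step describes what would happen if each ward were judged by its own significance. The article does not say that it will do so.

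**The case against.** The strongest reply is that a pooled analysis may well be intended. The Abstract compares 200 patients between two groups, the sample size is given as a total, and the H3 ANOVA is described without a split by ward. This stands. A reader might infer that no analysis uses the 200 patients, but the article does not support that. It is ambiguous between pooled and separate analysis, and the fault is that its sections point in different directions.

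A reader might also infer that cross-comparison means setting one ward's p-value beside the other's. The text does not say this, and it promises effect sizes with all results. Step 5 of the working is therefore a reason to specify the comparison, not a description of what is planned.

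Third, H3 may be secondary. The Measures section ties the primary hypotheses to clinicians' usability and acceptance, and calls the effect on patients a secondary objective. The Introduction lists H1 to H3 and then refers to them together as primary. The status of H3 is thus unclear, which limits how much weight the shortfall carries. It does not remove the shortfall, because the patient sample size is justified by this calculation.

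Finally, the 51% rests on a correlation that the article does not give. That is true, but 0.5 is the value that returns the article's own 200. An unseen full protocol or SAP might settle the matter, yet the conflict lies in what the article itself states.

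**Conclusion.** The point holds as an internal conflict. The calculation is not wrong: 200 patients in one analysis give the stated power (0.804) if ρ is about 0.5. What does not hold is the claim of 80% power for the reporting unit named under Study design. With the same inputs, each ward of 100 has about 51% power (0.39 at ρ = 0.3, 0.72 at ρ = 0.7), and the difference in change detectable with 80% power rises from 0.40 to 0.57 SD.

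This rests on f = 0.10, 1:1 allocation, complete data and the inferred ρ. It concerns the two-measurement analysis of H3. It does not show that a pooled analysis is absent from the plan.

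**What to change.** Reconcile the Study design section with the sample size paragraph:

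1. Name one pooled analysis of all 200 patients, adjusted for ward, as the main H3 test (the arm × time effect).
2. Report ward-specific estimates with confidence intervals as secondary.
3. Assess generalizability by the difference between wards in the treatment effect (the ward × arm × time estimate with its confidence interval), not by whether each ward is significant.
4. State the correlation of 0.5. Say that 0.80 applies only to the pooled H3 test under that value, and that each ward alone has about 51% power.

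The cost is wording and a less favourable stated power per ward. No extra patients are needed.

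The contrast in item 3 will be imprecise, and the text should say so. At ρ = 0.5 the SD of change equals the SD at one time point. The standard error of the treatment effect is then √(1/50 + 1/50) = 0.20 SD in one ward, and √(0.20² + 0.20²) = 0.28 SD for the difference between wards. The 95% interval is about ±1.96 × 0.283 = ±0.55 SD.

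If the sponsor wants each ward to stand as a confirmatory report, the alternative is to size each ward on its own. With the same inputs that means 200 patients per ward, twice the planned enrolment. It would use up the whole eligible pool of 400 that the article describes, and its feasibility is not shown.

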**Figure 1. fig1-20552076221129068:**
[figure not shown]
Study design.

At the enrollment (T1), patients will fill out the baseline questionnaires
collecting patient demographic information, and assessing their perceived
quality of life. The perceived quality of life is again measured at the end of
the intervention (T2).

Each patient will be followed for three–five days, depending on the standardized
care. During this period, health care quality measures, including health quality
measures, blood pressure, oxygenation and heart rate, and pain, are collected
for both groups two times a day. Blood pressure, oxygenation, and heart rate are
measured in all in-patients, recorded daily (standard procedure) and recorded on
a progression chart. In the intervention group, blood pressure, oxygenation, and
heart rate measures are stored electronically and the CDSS is used to flag
deviations from the standard, and alert the treating clinician. In the control
group, the standard progression chart is used as per hospital protocol. The
treating clinician is autonomous to decide to step up or modify antihypertensive
treatment. Pain is measured in all in-patients on daily basis, two times a day
(standard procedure), and recorded on a progression chart. In the intervention
group, the pain level is stored electronically and CDSS is used to flag and
alert the treating clinician on pain levels identified above anticipated. In the
control group, the standard progression chart is used as per hospital protocol.
The treating clinician is autonomous to decide to step up or modify analgetic
treatment.

The participating clinicians will be asked to evaluate the clinical usability and
provide answers on their acceptance of the CDSS system five times during the
study (after the first iteration, after half a year, after the first year, after
a year and a half, and after the last iteration).

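### Patients are randomised by the clinician group that also receives the alerts and decides treatment, and the claimed blinding cannot apply to that group

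*Protocol article*

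**What the plan says.** All statements are in the protocol article, Study design, unless noted.

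- **Recruitment.** Clinicians are participants alongside patients: "vascular or thoracic diseases, and clinicians, will be recruited at the regional" university centre. Participants and recruitment defines them as those who take part in grand rounds on the two wards.
- **Allocation.** Consent comes first ("Those who will consent to participate in the study will participate for five" days), and these patients then "will be randomized by the clinicians into" the intervention or control group.
- **Blinding.** "Blinding will be achieved by handling the same tools during the grand rounds". The next sentence begins "However, in the control group, the robot and tablet will not provide any" and goes on to say that it is information to clinicians that is withheld. Paper progression charts are kept for all patients in both groups as a further blinding measure.
- **Intervention group.** For pain, "the pain level is stored electronically and CDSS is used to flag and" alert the treating clinician. Blood pressure, oxygenation and heart rate are handled in the same way.
- **Control group.** In the "control group, the standard progression chart is used as per hospital protocol".
- **Treatment.** In both groups the treating clinician decides freely whether to change antihypertensive or pain treatment.

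**The concern.** Randomisation protects the comparison only if the person enrolling or assigning a patient can neither foresee nor influence the next assignment. Here the article gives the task to a group with a direct part in the trial. A clinician who knows or controls the next assignment may, even without intent, place patients with an easier expected course in one group. That would bias the between-group comparisons for health quality measures (H2) and quality of life (H3), and no later analysis reliably removes it.

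The blinding claim is a separate matter. Clinicians who know the group can change care in ways other than acting on an alert, and such changes cannot be separated from the effect of the system. The Discussion promises rigorous, high-quality evidence. A report that repeated the blinding claim without limits would lead readers to assume a protection that the trial does not have for its treating staff.

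**Working it through.** This is mainly a comparison of statements. No figure in the article bears directly on it.

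**1. Who does what.** The article names one body of clinicians and gives it these tasks: randomise patients, take part in rounds, receive alerts and decide treatment. It names nobody outside that body for allocation. That the same individuals do all of this is a close inference from the wording, not stated person by person.

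**2. Order of events.** Consent precedes randomisation. This limits refusal after assignment is known, but it does not prevent foreknowledge or steering. The text does not say whether the baseline questionnaires (T1) come before or after assignment.

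**3. What a clinician observes at the round.**

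| | Intervention | Control |
|---|---|---|
| Robot and tablet present | yes | yes |
| Paper chart kept | yes | yes |
| Output or alert to clinician | yes | none |

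The first two rows are the basis of the blinding claim. The third row differs between groups and identifies the group to the clinician. The claim therefore cannot cover clinicians. The article does not say whom it is meant to cover.

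**4. Which outcomes are exposed.** H2 measures respond to treatment decisions made by clinicians who know the group. Pain (visual analogue scale) is subjective, as is quality of life (EQ-5D-3L), so both could shift if patients can tell their group. The exploratory question R1 rests on clinicians' notes. The assessor of blood pressure, oxygenation and heart rate is not named.

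**5. Scale, as illustration only.** The planned total of 200 is reproduced with f = 0.10, two groups, m = 2 measurements and an assumed correlation of 0.5:

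- λ = f²·N·m/(1 − ρ) = 0.01 × 200 × 2/0.5 = 8, power 0.804.
- In change-score terms λ = N·d²/4, so d = √(4 × 8/200) = 0.40 SD.

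Suppose the true effect is zero and allocation adds a shift b in SD units. In a simple two-mean test with n per group, SE = √(2/n), and the two-sided error is P(|Z| > 1.96) with Z centred at b/SE.

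| n per group | SE | b = 0.1 | b = 0.2 |
|---|---|---|---|
| 100 (wards pooled) | 0.141 | 0.109 | 0.293 |
| 50 (one ward, equal allocation assumed) | 0.200 | about 0.08 | about 0.17 |

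The second row is closer to the plan, because the two cohorts are to be reported separately with 100 patients each. The shifts are assumed, and the test is not the growth-curve analysis planned for H2. The table shows only that a bias well below the 0.40 SD target would matter. It is not evidence that one exists.

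**The case against.** The strongest reply is that randomisation by clinicians may only describe who operates a concealed procedure, and that an article may leave sequence generation and concealment to the full protocol. The second part stands: missing detail is not the point here. The point is that the article positively assigns the task to an involved group, and its wording should not do so if the procedure is independent.

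It can also be said that clinicians' knowledge of the group is inherent in a system that works by alerting them. That stands too. The lack of blinding is not an avoidable fault, but the claim still needs correcting.

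A reader might infer more than the article supports:

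- **That there is no blinding at all.** The same robot and tablet at every round may partly mask patients, and the article does not rule this out.
- **That outcomes are recorded on paper in one group and electronically in the other.** The article charts all in-patients on paper, so electronic storage in the intervention group reads as an addition, not a contradiction.
- **That the control group is misdescribed.** The abstract's shorthand is "200 patients will be randomized into a Control Group (i.e. standard care) and an" intervention group, but Study design openly states that the silent robot and tablet are present.
- **That clinicians' ratings of the system are biased by knowing the group.** H1 compares clinicians with themselves over time and has no control group, so blinding to group does not bear on it.
- **That vital signs are measured with bias.** This is possible but not shown, since the assessor is not named.

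**Conclusion.** The point holds in two parts, both resting on stated rules and not on omissions. First, allocation is assigned to the clinician group that receives the alerts and decides treatment, which leaves selection bias open for H2 and H3. Second, the blinding claim cannot apply to clinicians; at most it describes partial masking of patients.

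The size of any bias cannot be derived from the article, and the error rates in the illustration must not be quoted as findings. The conclusion assumes that the randomising clinicians belong to the treating group, which the wording strongly suggests, and that no independent allocation procedure overrides the text. If the full protocol has such a procedure, the first part reduces to correcting the wording; the second part is unaffected. Allocation bias cannot be reliably repaired in the analysis, so this should be settled before patients are enrolled.

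**What to change.** 1. Replace randomisation by clinicians with a concealed allocation generated independently of the treating team and released only after consent and completion of the T1 questionnaires, for example by a web tool or a list held outside the wards. It can be stratified by ward, because the two cohorts are reported separately.
2. State that clinicians are unblinded. Limit any blinding claim to patients, described as partial, and to the analyst if the analyst is in fact masked.
3. As a supporting step, take the H2 values in both groups from the paper progression chart kept for every patient, so that the data source is the same in both.

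The cost is a short amendment, set-up of an allocation list or web tool, and some data entry from paper charts. Sample size and planned tests need not change on this account.
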